## Discussion

3

This study aims to (1) evaluate the efficacy of adjunctive VRCT in improving cognitive function in MCI, and (2) investigate potential brain-gut axis mechanisms mediating intervention effects through multimodal biomarker analyses.

Virtual reality cognitive training, as a demand-adapted cognitive training approach, offers an effective alternative that addresses several limitations of TCT, such as its time-consuming and labor-intensive nature (De Luca et al., 2020). Previous studies have suggested that VRCT may help delay or prevent dementia in high-risk middle-aged populations (Doniger et al., 2018). This effect is thought to stem from its capacity to enhance cognitive reserve and promote neuroplasticity (Teo et al., 2016). Furthermore, VRCT provides immersive and interactive experiences by simulating real-world environments, effectively integrating cognitive and physical training components (Stone et al., 2011). We hypothesize that this unique feature may compensate for the limitations of TCT and enhance its efficacy.

Recent evidences suggest that cognitive impairment is associated with specific gut microbial communities (Aljumaah et al., 2022; Kesika et al., 2021; Tooley, 2020). This finding suggests that cognitive decline may be improved through interventions such as probiotics, prebiotics, and commensal bacteria. Indeed, a recent meta-analysis indicates that probiotic supplementation may enhance cognitive function, particularly among individuals with MCI (Zhu et al., 2021). Moreover, brain imaging studies have provided evidence that gut microbiota are associated with alterations in brain structure and function (Tooley, 2020), further supporting their relationship with cognition. However, although cognitive training has been shown to improve cognition, few studies have explored its role in influencing the brain-gut axis. We hypothesize that adjunctive VRCT may mediate cognitive improvement in patients with MCI by influencing gut microbial composition, metabolic profiles, and brain function and structure. However, this hypothesis remains inconclusive. To explore potential neurobiological associations, we will collect multimodal data, including MRI, serum metabolomics, gut microbiomics, and comprehensive cognitive assessments.

This study has several limitations. First, the study population comprised individuals with MCI, a highly heterogeneous group that may progress to diverse dementia subtypes over extended observational periods. Given the time-limited nature of our cognitive training intervention, we were unable to evaluate whether the combined intervention delays dementia onset. Second, this is a single-blinded study, so there may have been a placebo effect interfering with the experimental results. However, we will blind the raters and statisticians to minimize potential bias. Third, our study population consisted of older adults, and the potential presence of comorbid conditions may have influenced the experimental outcomes. We will analyze the impact of these comorbidities as potential confounding factors in our results. Fourth, It is important to acknowledge that the multi-modal nature of our intervention introduces potential non-specific effects. The intervention group received enhanced social interaction, professional guidance, and exposure to novel technology, which may have contributed to the observed outcomes through psychosocial mechanisms such as the placebo effect or Hawthorne effect. While these elements are integral to the real-world delivery of such an intervention, future studies with dismantling designs could help isolate the specific contribution of each component. Fifth, we adopted square dancing as the form of physical exercise primarily to enhance participants’ engagement and adherence, although individual variations in exercise intensity may exist. Moreover, square dancing is deeply rooted in specific cultural and regional contexts, which may hinder its adoption and effectiveness in other geographical or cultural settings. Sixth, although the MoCA was initially registered as the primary outcome, we subsequently adopted a memory-weighted cognitive composite as the revised primary outcome to provide greater sensitivity for detecting subtle cognitive changes over the 24-week trial period. Finally, some elderly participants may experience discomfort when wearing virtual reality equipment for extended periods. To address this, we intentionally incorporated a mind-body relaxation section to help reduce tension and improve comfort.

In summary, this study investigates the efficacy of adjunctive VRCT in individuals with MCI, along with its underlying brain-gut axis mechanisms. If effective, this combined VRCT approach may offer an accessible, non-pharmacological strategy for preventing dementia progression in community-dwelling older adults. Our findings may contribute novel insights to this emerging field and inform the development of innovative therapeutic strategies to slow dementia progression.

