We hypothesize that a multi-modal intervention, integrating VRCT, TCT, and PE, will improve cognitive performance and beneficially modulate the brain-gut axis in individuals with MCI. To test this hypothesis, we will conduct a randomized, single-blind controlled trial among community-dwelling older adults with MCI. The primary objective of this study is to investigate whether the multi-modal intervention enhances cognitive function in community-dwelling older adults with MCI. The exploratory objective is to characterize the underlying brain-gut axis mechanisms, as assessed by resting-state functional MRI and 16S rRNA gene sequencing of the gut microbiota.

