### Study design

2.1

This single-blind, randomized controlled trial (ChiCTR2400093397, www.chictr.org.cn) employs a two-arm parallel design, consisting of an intervention group receiving a combination of VRCT, TCT, and PE, and a waitlist control group who will receive no training during the research period. As compensation, the waitlist group will be offered the same training after the follow-up assessment. All participants will undergo comprehensive assessments at four time points: baseline (week 0), mid-intervention (week 6), post-intervention (week 12), and a 12-week follow-up (week 24). The trial is designed in accordance with the CONSORT (Consolidated Standards of Reporting Trials) guidelines and will be conducted and reported accordingly.

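### The Discussion states the aim, hypothesis and summary as the efficacy of adjunctive VRCT, but the objective and two-arm design address only the combined VRCT+TCT+PE package against a waitlist

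*Protocol article*

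**What the plan says.** The protocol article states its question in two ways.

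- **Package level.** The Introduction says that the primary objective is to "investigate whether the multi-modal intervention enhances cognitive function in community-dwelling older adults with MCI". Section 2.1 describes "an intervention group receiving a combination of VRCT, TCT, and PE" and "a waitlist control group who will receive no training during the research period". The abstract and section 2.7 agree. Section 2.8.2 analyses the primary outcome with group, time and their interaction.
- **VRCT level.** The Discussion opens with the aim to "evaluate the efficacy of adjunctive VRCT in improving cognitive function in MCI". It later says "We hypothesize that adjunctive VRCT may mediate cognitive improvement in patients with MCI", by way of gut microbes, metabolic profiles and the brain. It also suggests that VR's immersive character could make up for weaknesses of TCT and strengthen its effect. The closing paragraph begins: "In summary, this study investigates the efficacy of adjunctive VRCT in individuals with MCI".

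The fourth limitation, also in the Discussion, concedes that a multi-modal intervention brings non-specific effects and leaves the contribution of each component to future dismantling studies.

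**The concern.** In a programme made of VRCT, TCT and PE, adjunctive VRCT can only mean VRCT added to the other two. That is a different question from whether the whole programme beats no training, and this trial is built to answer only the second.

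What is at stake is the claim that a positive result may carry. The Introduction itself cites evidence that TCT and PE can slow cognitive decline in MCI. On the article's own account, then, a difference from the waitlist could arise with no contribution from VRCT. Read against aim (1), the same difference would be credited to VRCT.

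**Working it through.** No figure in the plan quantifies an added effect of VRCT, so the check compares the contrast that the Discussion names with the contrast that the design supplies.

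**1. Arms.** Sections 2.1 and 2.3 give two arms, randomised 1:1: VRCT+TCT+PE, and a waitlist with no training. No arm receives TCT+PE alone, and none receives VRCT alone.

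**2. Contrasts.** Write μ for the mean change in the primary composite under each regimen.

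- Estimated by the trial: Δ(package) = μ(VRCT+TCT+PE) − μ(waitlist).
- Named in the Discussion: Δ(adjunctive) = μ(VRCT+TCT+PE) − μ(TCT+PE).
- Their relation: Δ(package) = Δ(adjunctive) + [μ(TCT+PE) − μ(waitlist)].

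The trial estimates the left-hand side. Both terms on the right are unknown, and μ(TCT+PE) is observed in no arm. One equation with two unknowns has no unique solution. More participants would sharpen Δ(package) and leave the split as undetermined as before.

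**3. Variation within the intervention arm.** Sections 2.4.1 to 2.4.3 schedule all three components for every intervention participant at each session: PE, then TCT, then VRCT. The random draw at each session selects which TCT task and which VRCT task is used. It does not decide whether VRCT is given. The plan therefore creates no randomised contrast in exposure to VRCT inside the arm.

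**4. Analysis.** The group-by-time interaction in section 2.8.2 compares the two arms over time, so it is a package-level test. Nothing in the model is specific to VRCT.

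**5. Sample size, to see whether it bears on the point.** Section 2.8.1 gives f = 0.25, α = 0.05, 90% power, a minimum of 46 and 66 enrolled. The number of measurements m and their correlation ρ are not stated. Assuming a within-between interaction with m = 2 and ρ = 0.5:

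- λ = N·m·f²/(1−ρ) = 46 × 2 × 0.0625 / 0.5 = 11.5, with 1 and 44 degrees of freedom, which gives power 0.912.
- 46 / (1 − 0.30) = 65.7, rounded up to 66.

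Both figures reproduce under these assumptions. They concern a comparison of the two arms that exist, so the sample size neither supports nor harms the adjunctive claim.

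**6. Text against text.** The Introduction's objective matches Δ(package). Aim (1), the mediation sentence, the suggestion that VR strengthens TCT, and the first sentence of the summary all match Δ(adjunctive). The fourth limitation, which sits between that aim and that summary, accepts that components are not isolated.

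**The case against.** The best defence is that this is loose labelling in a narrative section. Much of it stands. The formal objective, abstract, design, procedure and primary analysis all put the question at package level. The summary goes on to speak of a combined approach, aim (2) refers to intervention effects in general, and the inability to separate components is printed as a limitation. The added effect of VRCT is never written into a hypothesis test.

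This narrows the point but does not remove it. The limitation confirms that the design cannot deliver aim (1), while the statements before and after it remain as they are. Nor is this a detail that an article leaves to a fuller document: it is a positive statement of aim that conflicts with the article's own objective.

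Four stronger readings are tempting, and the documents do not support them.

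- A reader might infer that the whole trial is planned around a question it cannot answer. The Introduction and sections 2.1 and 2.8 show otherwise.
- A reader might infer that the planned mediation analysis is specific to VRCT. Section 2.8.2 asks whether brain-gut changes drive clinical improvement and names no VRCT exposure. The Discussion itself calls its own hypothesis inconclusive.
- A reader might infer that a positive result will be reported as evidence for VR. That is a risk created by the wording. No results claim has been made.
- A reader might try to size VRCT's share, either as some fraction between none and all of the observed difference or by its share of session time. The first needs an unstated assumption that no component does harm or interacts with another. The second says nothing about effect, and section 2.4.3 does not settle whether the 5-minute relaxation lies inside the 15 minutes.

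**Conclusion.** The point holds as an internal contradiction limited to the Discussion. Aim (1), the VRCT-specific hypotheses and the opening of the summary name an effect that the design cannot identify, and they conflict with the primary objective in the Introduction.

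The size is not numerical: the added effect of VRCT has no estimate and no bound from this trial, whatever the number enrolled. The conclusion rests on reading adjunctive as VRCT added to TCT+PE. If it is read as VRCT by itself against no training, the result is the same, because no arm receives VRCT alone. The sample size, primary analysis and conduct of the trial are not in question here. The correction should be made because it settles, before results are known, what a positive finding may be said to show.

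**What to change.** Reword three places in the Discussion: aim (1); the VRCT-specific hypotheses (that VRCT mediates improvement, and that it strengthens TCT); and the first sentence of the summary. Each should refer to the effect of the combined VRCT+TCT+PE programme versus waitlist, in line with the Introduction. Add one sentence, for example beside the fourth limitation, stating that no conclusion on the added value of VRCT will be drawn from this trial.

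The cost is wording and a narrower claim. No arm, endpoint, analysis or sample size changes.

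Keeping the adjunctive aim would instead need a TCT+PE comparator and a new sample size. The documents give no add-on effect, so the following is illustration only. By the normal approximation (two-sided 0.05, 90% power), n per arm = 2(1.960 + 1.282)²/d². An assumed d = 0.5 needs 85 per arm, or 170 evaluable and 170/0.7 → 243 enrolled. An assumed d = 0.3 needs 234 per arm, or 468 evaluable and 468/0.7 → 669 enrolled. Rewording is the proportionate remedy.
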